# Assessing the effectiveness of dialkylcarbamoylchloride (DACC)-coated post-operative dressings versus standard care in the prevention of surgical site infection in clean or clean-contaminated, vascular surgery (the DRESSINg trial): study protocol for a pilot feasibility randomised controlled trial

**DOI:** 10.1186/s40814-019-0400-2

**Published:** 2019-01-18

**Keywords:** Infection, Surgery, Surgical wound, Dialkylcarbamoylchloride, DACC, Prevention

## Abstract

**Background:**

Surgical site infection in vascular surgery has a reported incidence of up to 19%. A novel method of reducing this rate of infection is dressings coated with dialkylcarbamoylchloride (DACC), a hydrophobic wound contact layer that binds bacteria and removes them from the wound bed. Early research has suggested that DACC-coated wound dressings are effective in reducing surgical site infection when applied to wounds healing by primary intention post-operatively, therefore this trial aims to assess the feasibility of producing high-quality evidence assessing this theory.

**Methods:**

Patients undergoing clean or clean-contaminated vascular surgery will be randomised to have their surgical wounds dressed with a DACC-coated dressing or a non-coated occlusive absorbent post-operative dressing. All other aspects of their peri-operative care will be standardised or carried out in line with hospital policy. Wound assessments will be carried out between day 5–7, day 30 (± 3 days) and 6 months post-operatively (± 7 days) by a blinded assessor using the ASEPSIS scoring tool. Quality of life data using EQ-5D and SF-36, resource use and mortality data will also be collected. This feasibility trial will dictate the conduct of a full-scale trial through the collection of data on recruitment and retention rates, and fitness-for-purpose of the follow-up arrangements.

**Discussion:**

Surgical site infections are now the second most common hospital acquired infections with a significant cost implication. The aim of the DRESSINg trial is to investigate the effectiveness of a novel preventative measure at reducing wound infections post-surgery and will provide robust evidence to support or deny its use.

**Trial registration:**

Clinicaltrials.gov identifier: NCT02992951, Registered 12/12/16. REC Reference: 16/LO/2135.

## Introduction

The Centres for Disease Control and Prevention (CDC) defines a surgical site infection (SSI) as an infection within 30 days of an operation or up to 90 days if an implant is left in place and the infection is related to an operative procedure [1]. SSI’s occur in at least 5% [2] of patients and have a significant impact on patient morbidity, mortality and have subsequent time and cost implications [3].

Microorganisms causing SSI’s may be either endogenous (present on the patient) or exogenous (from the environment). The most common bacteria causing a superficial wound infection are those which are present on the skin of the patient. Deeper wound infections may be due to contamination of the wound by bacteria encountered during a procedure. Despite the reported incidence of SSI’s for clean surgery of 2.1% [4], the incidence in practice varies significantly. Open varicose vein surgery has an incidence of SSI’s reported in the literature which varies from 1.5 to 16% [5, 6] whilst figures from the surgical site infection surveillance demonstrated a high rate of SSI’s in patients undergoing lower limb amputation (13.1%) [7]. Conversely, SSI rates following carotid endarterectomy are reported as low as 0.2% [8, 9].

The Sorbact® range of dressings contains dialkylcarbamoylchloride (DACC), found in a spider’s web, which mediates the irreversible binding of bacteria that exhibit a high cell surface hydrophobicity (CSH). Large numbers of adherent or ‘trapped’ bacteria can then be removed from the wound at each dressing change. They are removed without disrupting the bacterial cell wall, thereby avoiding the resultant increase in inflammation observed with traditional antibiotics or antiseptics [10]. Numerous bacteria and fungi that exhibit CSH have been shown to attach to the DACC-coated material, including *Staphylococcus aureus*, *Pseudomonas aeruginosa*, *Enterococcus faecalis*, *Candida albicans* and the dermatophyte *Trichophyton rubrum* [11, 12].

DACC-coated dressings are available on the open market in both the UK via the National Health Service (NHS) supply chain, and the USA [13].

The current available evidence, although limited, favours the use of DACC-coated dressings in reducing SSI [14]. A recently published randomised controlled trial and preceding pilot study concluded that in a cohort of women undergoing caesarean section in a single centre, DACC-coated dressings proved to be clinically and cost-effective in reducing the rates of SSI [15, 16], indicating that further high-quality studies are needed in this promising area to assess outcomes in a more diverse patient population.

## Methods/design

### Study objectives

The aim of this pilot randomised trial is to evaluate the feasibility of conducting a fully powered randomised controlled trial to investigate the effectiveness of DACC-coated post-operative dressings in the reduction of surgical site infection in vascular surgical patients, using a fraction (one-fifth) of the patients required for a fully powered RCT.

### Study design and setting

This is a pilot feasibility randomised single-centre clinical trial in the setting of a University Teaching Hospital, based in the UK, offering tertiary vascular surgery services. The protocol has been prepared in line with the Standard Protocol Items: Recommendations for Interventional Trials (SPIRIT) guidelines [17].

### Inclusion criteria

The inclusion criteria are:Over 18 years of ageUndergoing clean or clean-contaminated vascular surgery (as opposed to contaminated or dirty surgery, in which there is infection already present).Able to understand (i.e. have sufficient language skills) and complete the patient information sheet, consent forms, and questionnaires.Able and willing to give informed consent to participate in the trial (patients may be capacitous but unwilling to give informed consent; they would not meet the inclusion criteria).

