### Sample size calculation

The incidence of SSI’s following clean and clean contaminated, non-implant surgery varies widely between the procedures to be included in this study. Whilst the overall infection rate is quoted as being 2.1–3.3%, this is predominantly based on the findings of Cruse and Foord [27] following their long-term surveillance. This has been criticised as it predominantly relies on questionnaire follow-up, over the phone at day 28 post-surgery. The reality in practice is that the infections rates are much higher and are more frequently diagnosed when examined by a blinded observer [28].

The power calculation is based on the primary endpoint having a 90% power and 5% significance. A non-randomised prospective trial comparing Leukomed® Sorbact® with standard dressings in non-implant, clean or clean-contaminated vascular surgery patients, carried out in the same centre demonstrated an overall reduction in SSI from 19 to 10% [29]. To demonstrate the same reduction in SSI, a sample size of 320 per group, or a total of 712 patients, allowing for a 10% loss to follow-up, is required. Study retention rates will be examined at the first interim analysis, and the power calculation amended accordingly. With such a large sample size, there is a high potential for larger loss to follow-up rates than initially expected. Therefore, this pilot study will aim to recruit one-fifth (144) of the total patients needed. The results of this pilot trial, along with other published data on DACC in the reduction of SSI, will be combined to produce a final power calculation for a full-scale RCT.

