### Recruitment

Patients that are referred for a clean or clean-contaminated vascular surgical operation will be considered for the study. Patients may be identified at their initial outpatient appointment, at pre-assessment clinics or on their admission to the ward. Patients admitted on a semi-elective or emergency basis will be identified as they are admitted to the ward. Suitable patients will be made aware of the study and provided with the appropriate information, including the patient information sheet. Following this, patients that express an interest will be invited to a screening visit with a study investigator. For inpatients, this visit may take place on the inpatient ward. At this appointment, patients will be assessed against the inclusion and exclusion criteria, and if potential participants meet said criteria, informed consent to participate in the trial will be taken by a study doctor and recorded on the informed consent form and in the patient notes.

To ensure confidentiality and to adhere to data protection guidelines, participants will be given a unique identifying number which does not allow for the identification of study arms or demographic information. The identifiable patient information will not be available to any person(s) outside of the research group. The patient’s general practitioner will also be informed of study enrolment and study details. No changes to concomitant medications will be made, and no restrictions to trial treatments or methods based on concomitant treatment will be made.

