### Statistical analysis

Data will be analysed on an intention to treat basis. The SPSS (IBM Corporation, Armonk, NY, USA) computer package will be used with a two-sided *p* value of < 0.05 taken as the level of significance. For feasibility outcomes, simple categorical data will be presented descriptively using mean (SD), median (IQR) for skewed data or *n* (%) for each group. Recruitment of a large trial within 18 months (based on rates observed in the pilot trial), and retention of 85% or better will be deemed acceptable.

Descriptive statistics (mean (sd) and *n* (%)) will be calculated for demographic and baseline characteristics of the patients. For the clinical outcome of SSI at 30 days, logistic regression analysis will be undertaken with SSI as the dependent variable and randomisation group as the independent variable. The model will be adjusted for confounding variables such as sex, age, BMI, smoking status, diabetes status and surgical site, as well as implant vs non-implant surgery. The regression model performance will be assessed by the Hosmer and Lemeshow test. Logistic regression will also be undertaken for satisfactory healing—total ASEPSIS score ≤ 10. For quality of life (EQ-5D-3 L and SF-36), an intragroup and intergroup analysis will be performed, using Friedman’s two-way analysis of variance (ANOVA) test to assess for intragroup differences, and Mann-Whitney *U* tests to assess for intergroup differences of the SF-36 responses. For the EQ-5D, responses will be dichotomised into ‘no problems’ and ‘problems’, and intragroup analysis conducted using related sample’s Cochrane’s Q test, with Pearson’s χ^2^ tests for intergroup analysis. For time to event data (time to return to work and mortality), Kaplan-Meier and long rank tests will be used to calculate and compare event rates between groups, followed by a cox regression to adjust for confounding variables.

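### Willingness to consent is written into the inclusion criteria and the criteria are formally checked only after interest is shown, so the eligibility rate and recruited/eligible may misclassify refusals

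*Protocol article*

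**What the plan says.** Four places in the Protocol article bear on this.

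- **Inclusion criteria.** Being able and willing to consent is one of the criteria. The text then adds a classification rule: "patients may be capacitous but unwilling to give informed consent; they would not meet the inclusion criteria".
- **Recruitment.** Referred patients are considered for the study. Then "Suitable patients will be made aware of the study and provided with the appropriate information, including the patient information sheet", and after that "patients that express an interest will be invited to a screening visit with a study investigator". The formal check comes at that visit: "At this appointment, patients will be assessed against the inclusion and exclusion criteria". Consent is taken from those who meet the criteria.
- **Feasibility outcomes.** Eligibility rates with reasons for non-eligibility are one item, and recruitment rates with reasons for non-recruitment are another. A further item asks whether the inclusion and exclusion criteria are suitable. No denominator is given for any rate.
- **Statistical analysis.** Two results are deemed acceptable for feasibility: "Recruitment of a large trial within 18 months (based on rates observed in the pilot trial"), and retention of at least 85%. No threshold is set for the eligibility or consent proportion.

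**The concern.** A pilot needs to separate two reasons for not enrolling a patient: the criteria exclude the patient, or the patient could take part and says no. The responses differ. The first calls for a look at the criteria, the second for a look at how patients are approached. The Feasibility outcomes section keeps the two apart, but the rule in the Inclusion criteria merges them by making a refusal a failure to meet the criteria.

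The order of events in the Recruitment section adds a separate problem. A patient who shows no interest is not invited to the visit where the criteria are applied, so nothing described in the article establishes whether that patient would have been eligible.

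At stake are the eligibility rate, the proportion of eligible patients recruited, and the judgement on whether the criteria are suitable. Feasibility is the stated aim of the trial, so these are named outputs.

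**Working it through.** **Inputs.** The article states no eligibility rate and no consent rate, so two quantities are assumed: *e*, the share of patients considered who meet every criterion other than willingness, and *w*, the share of those who agree. From the article come the pilot target (144), the recruitment period (18 months) and the full-trial size (320 per group, 712 in total).

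**The plan's own figure.** The only related figure that can be reproduced is the sample size, with 19% versus 10%, two-sided 5% significance and 90% power:

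n = [1.960·√(2·0.145·0.855) + 1.282·√(0.19·0.81 + 0.10·0.90)]² / 0.09² ≈ 319.6, so 320 per group.

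Allowing for 10% loss: 320/0.9 = 355.6, so 356 per group and 712 in total. It matches, and neither *e* nor *w* enters it.

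**Effect of the literal rule when refusals occur at the visit.**

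- Willingness kept out: eligibility = *e*; recruited/eligible = *w*.
- Willingness counted as a criterion: eligibility = *e·w*; recruited/eligible = *e·w*/*e·w* = 100%.

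With *e* = 0.8 and *w* = 0.5, eligibility is 0.8 × 0.5 = 40% instead of 80%, and recruited/eligible is 100% instead of 50%. Over *e* = 0.6 to 0.9 and *w* = 0.3 to 0.9, literal eligibility runs from 0.6 × 0.3 = 18% to 0.9 × 0.9 = 81%, instead of 60% to 90%. Recruited/eligible stays at 100% instead of ranging from 30% to 90%.

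**The two routes differ.** Take an assumed 300 patients considered, 240 meeting the other criteria and 144 recruited. Only the 144 comes from the article.

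| How patients decline and are counted | Eligibility | Recruited/eligible | Recruited/considered |
|---|---|---|---|
| Willingness kept out, all 300 assessed | 240/300 = 80% | 144/240 = 60% | 144/300 = 48% |
| All 300 reach the visit, 96 refuse there, literal rule | 144/300 = 48% | 144/144 = 100% | 48% |
| Only 180 show interest and are assessed, all who qualify agree | 144/180 = 80% | 144/144 = 100% | 48% |

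In the third row the eligibility rate comes out right only because interest is assumed unrelated to the other criteria (180 × 0.8 = 144). If it is related, the rate shifts in a direction the article cannot tell us. Early decliners in that row are not counted as ineligible; they drop out of the assessed group.

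**What does not move.** Recruited/considered is 48% in every row, and recruited/approached is likewise independent of the label once those approached are counted. Accrual at the planned pace is 144/18 = 8.0 per month under any labelling, against 712/18 = 39.6 per month to recruit 712 in 18 months. Retention concerns patients already enrolled.

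**The case against.** A reader might infer that the pilot's eligibility and recruitment rates are wrong by construction and that the decision on a large trial is compromised. The document does not support that, for these reasons:

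- **No denominator is fixed.** The 100% for recruited/eligible follows only if the literal rule defines the eligible group. The article does not say that it does.
- **Reasons are recorded.** A refusal at the visit logged as non-eligibility would carry unwillingness as its reason and could be moved back. This stands, but it does not help with patients who declined before the visit, for whom no formal assessment is described.
- **Criteria come before consent.** The Recruitment section takes consent after the criteria are met, and Table 1 puts the screening questionnaire at screening and consent at the baseline visit. A patient can therefore be assessed on everything else and then decline. That is true in practice, but the parenthesis in the Inclusion criteria still labels such a patient as not meeting them.
- **There may be an earlier sift.** Informing only suitable patients implies some selection before interest is sought, so eligibility is not clearly judged only afterwards. The word is undefined, and no record of that sift is described.
- **Progression is untouched.** Neither the 18-month recruitment criterion nor the 85% retention criterion depends on how decliners are labelled.
- **An article condenses the protocol.** The absence of a screening log or flow definitions is not held against it, and the flow chart is not available here. The point rests on the stated rule and the stated order of events.

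**Conclusion.** The point holds in a limited form. The Inclusion criteria class unwilling patients as not meeting the criteria, and the Recruitment section formally applies the criteria only to patients who have shown interest. This conflicts with reporting eligibility and recruitment as separate outcomes, and it blurs the question of whether the criteria are suitable. The eligibility rate and recruited/eligible may be misclassified.

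The size depends on *e* and *w*, which are assumptions, and on the rule being followed literally. Over the ranges shown, eligibility could read 18% to 81% where 60% to 90% applies, and recruited/eligible could read 100% where 30% to 90% applies. How the logs were actually kept cannot be checked from the article.

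The sample size, monthly accrual, recruited/approached, retention and both progression criteria are unaffected. This is a correction worth making to two named feasibility outputs, not a fault that invalidates the pilot.

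**What to change.** 1. Keep consent as a condition of enrolment, but take willingness, and the parenthesis about unwilling patients, out of the definition used to count eligibility.
2. Apply the criteria that can be judged from the referral or notes to all patients considered, before interest is sought. Some cannot be settled then, such as antibiotic use up to the day of surgery and the ability to complete the questionnaires; confirm these later and record at which stage a patient failed.
3. Count decliners, before or at the visit, as eligible but not recruited, with refusal recorded under reasons for non-recruitment. For early decliners this status rests on the criteria checked by then, and the report should say so.
4. Report eligible/considered and consented/eligible separately, each with its denominator.

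The cost is a short note review for each referred patient and a less favourable recruited/eligible figure. No extra participants or trial procedures are needed. The Trial status section describes recruitment as still active, so the change could apply to patients not yet considered; refusals already logged at the visit can be reclassified from their recorded reasons.

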### Exclusion criteria

The exclusion criteria are:Patients actively taking antibiotics for other conditions up to the day of surgery (not including surgical prophylaxis or antibiotic use related to the index procedure)Patients undergoing carotid endarterectomy (as these patients have an infection rate significantly lower than rates seen in other types of vascular surgeries [8, 9])Allergies to any component of either the DACC-coated dressing or the control dressingInability to give informed consent due to incapacity (as defined by the MCA 2005 [18])Aged under 18 years at the time of recruitmentUse of investigational drug/device therapy within preceding 4 weeks that may interfere with this study.

### DACC-coated post-operative dressings and post-operative procedures

Patients will receive standardised care pre-operatively. Hair removal (clipping) and anaesthesia will be conducted according to local hospital policy; in our centre, hair is clipped, not shaven, immediately prior to the procedure in the operating theatre. Skin preparation will be standardised to Povidone-iodine in aqueous solution, unless there is a documented patient allergy. Prophylactic antibiotics will be given as per local guidelines and recorded in the patient notes. Patients will be randomised on the day of their surgical procedure to receive post-operative dressing with a DACC-coated dressing (Leukomed® Sorbact®, BSN Medical, Hull, UK), or a non-coated occlusive absorbent control post-operative dressing (standard practice) (OpSite® Post-Op, Smith & Nephew, Hull, UK).

All dressings will be replaced on day 2 post-procedure, and again at the time of first wound review, which takes place between post-operative days 5–7. Interim dressing changes will be permitted where there is a clinical indication such as soiling or damage to the dressing. On discharge from hospital, patients will be provided with further dressings of the same variety to ensure like-for-like dressing changes up to the point of wound healing, as well as instructions to community teams that the only wound dressings to be used are the ones provided for trial purposes, in order to maintain treatment adherence.

### Outcomes

Outcomes will be divided into two sections: *feasibility outcomes* and *clinical outcomes*.

#### Feasibility outcomes

The measured effect size of the trial intervention, in order to contribute to the power calculation and design of a full scale RCTEligibility rates and reasons for non-eligibilityParticipant recruitment rates and reasons for non-recruitmentFollow-up and study retention rates and reasons for drop-out/non-attendanceFitness for purpose and acceptability of follow-up arrangementsThe suitability of the trial intervention in different wound types/areasThe suitability of the inclusion/exclusion criteriaThe suitability of outcome assessment measure(s)Fitness for purpose and acceptability of data collection methods, including the use of smartphone or online ‘apps.’Rates of participant withdrawal from the trial; participant response rates to questionnaires; likely rates of missing study data.

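### At 144 patients the pilot cannot support or deny effectiveness, and its effect estimate is too imprecise to be an input to the full-trial sample size

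*Protocol article*

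**What the plan says.** - **Study objectives** gives the aim as judging whether a fully powered trial is feasible, using one-fifth of the patients such a trial would need.
- **Feasibility outcomes** lists, before any other item, "The measured effect size of the trial intervention, in order to contribute to the power calculation" and design of the full trial.
- **Sample size calculation** sizes the full trial at 320 per group, 712 in total with 10% loss: "The power calculation is based on the primary endpoint having a 90% power and 5% significance". The planning effect is from a non-randomised study in non-implant patients, "carried out in the same centre demonstrated an overall reduction in SSI from 19 to 10" per cent. The pilot recruits 144. Its results, together with other published data on the dressing, "will be combined to produce a final power calculation for a full-scale RCT". No method of combination or weighting is given.
- **Statistical analysis** plans an adjusted logistic regression of 30-day SSI on randomised group, "with a two-sided *p* value of < 0.05 taken as the level of significance". The only acceptability criteria stated there are recruitment of a large trial within 18 months and retention of at least 85%.
- **Abstract, Discussion** says the trial "will provide robust evidence to support or deny its use". The main Discussion also gives the aim as investigating effectiveness.

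The document states no power or precision for the 144-patient pilot.

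**The concern.** The protocol asks the pilot for two things beyond feasibility: an effect size to help set the full-trial sample size, and evidence for or against the dressing. Both need a reasonably precise between-arm comparison, and the protocol's own calculation puts the number needed for that at 712, not 144.

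Two consequences follow. Required sample size varies roughly with the inverse square of the difference, so an imprecise pilot effect turns into a very imprecise sample size, and a chance overestimate yields an underpowered full trial. Also, a reader who takes the abstract at its word may treat a non-significant pilot result as evidence against the dressing. The only power figure in the document is 90%, which belongs to the full trial.

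**Working it through.** **Inputs (all from the protocol).** Control SSI 19%, DACC 10%, 5% significance, 90% power, 10% loss, 320 per group, 712 total, pilot 144 (Sample size calculation); two-sided testing and acceptable retention of 85% (Statistical analysis); equal allocation (Randomisation).

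**1. The plan's own figure.** With p1 = 0.19, p2 = 0.10 and mean 0.145:

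n = [1.96·√(2·0.145·0.855) + 1.2816·√(0.19·0.81 + 0.10·0.90)]² / 0.09² = 319.6, so 320 per group.

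640 / 0.9 = 711.1, so 712. The stated size reproduces; one-fifth is 142.4, rounded up to 144.

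**2. Pilot size.** 144 / 2 = 72 per arm; 72 × 0.90 = 64.8, about 65; 72 × 0.85 = 61.2, about 61.

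**3. Power and precision of the pilot.**

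Power = Φ{[0.09·√n − 1.96·√(2·0.145·0.855)] / √(0.19·0.81 + 0.10·0.90)}

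95% half-width = 1.96·√[(0.19·0.81 + 0.10·0.90)/n]

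| Basis | n per arm | Power | Half-width | Interval if 9 points is observed |
|---|---|---|---|---|
| No loss | 72 | 33.4% | 11.4 points | -2.4 to +20.4 |
| 10% loss | 65 | 30.6% | 12.0 points | -3.0 to +21.0 |
| 15% loss | 61 | 29.0% | 12.4 points | -3.4 to +21.4 |

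Exact enumeration at 65 per arm gives 30% power for the uncorrected chi-square test and 23% for Fisher's test. Expected SSIs are 65 × 0.19 = 12.4 and 65 × 0.10 = 6.5. On the scale of the planned logistic regression (unadjusted), the odds ratio is (0.10/0.90)/(0.19/0.81) = 0.47, with an approximate 95% interval of 0.17 to 1.31.

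**4. What that interval means for sizing.** Holding control at 19% and 90% power, reductions of 6, 9 and 12 points need 783, 320 and 163 per group. All three lie well inside the pilot's interval.

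**5. Bounding case: full trial sized on the pilot estimate alone.** This is not quite the plan's procedure; it shows how little the estimate carries by itself. All outcomes at 65 per arm were enumerated with true rates 19% and 10%, and the formula in step 1 was applied to each observed pair of rates.

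- Chance of no apparent benefit: 8.8%.
- Chance of overstating the effect by at least half (13.5 points or more): 25%.
- Implied n per arm: 10th percentile 94, median 318, 75th percentile 1,119.
- True power of 80% needs about 239 per arm; the implied n falls below this in 42% of pilots.
- True power of 50% needs about 118 per arm; the implied n falls below this in 17% of pilots.

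**6. What the pilot estimates better.** The SSI rate pooled over arms, at 14.5% in 130 patients, has half-width 1.96·√(0.145·0.855/130) = 6.1 points, about half that of the difference. It also describes the implant and non-implant mix actually enrolled, which the 19%-to-10% study does not.

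**The case against.** The strongest reply is that the plan does not size the full trial on the pilot alone. The effect is to contribute, and it is to be combined with other published data; the Introduction cites a randomised trial and its pilot in caesarean section. This stands. The 42% and 17% figures describe a procedure the protocol does not state, and with no weighting given the real mis-sizing risk cannot be calculated. It does not rescue the estimate, however. Combination dilutes the pilot's noise without making its own effect informative, and the sources named differ from this trial in population (caesarean section) or in design and population (non-randomised, non-implant).

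A reader might infer that the protocol sets a p < 0.05 rule for supporting or rejecting the dressing. It does not. The significance level and the abstract's claim are in separate sections, and nothing joins them. A reader might also infer that the dressing could be abandoned on a chance null result. No text makes progression depend on SSI significance; the stated criteria concern recruitment and retention only.

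It is also fair to say that the abstract's sentence is outweighed by the feasibility aim in Study objectives, and that it may describe the wider programme, since the document elsewhere speaks of a pilot phase. That makes it overclaiming rather than a design error, but the sentence as written is about this trial, and the main Discussion repeats the effectiveness aim. Finally, the protocol never claims 90% power for 144 patients, and it treats 712 as provisional.

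**Conclusion.** The concern holds in a limited form. On the protocol's planning rates the pilot has about 31% power and a ±12-point interval after 10% loss (33% and ±11.4 points with no loss). It therefore cannot support or deny effectiveness, and its between-arm estimate is too imprecise to drive a sample size. These figures assume true rates of 19% and 10%, from a non-randomised study in non-implant patients; the rates in the enrolled mix may differ.

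The 42% chance of a full trial with under 80% true power applies only if the pilot estimate is used alone, and should not be read as the plan's actual risk. The calculation of 320 per group is correct, and the documents support neither a significance-based decision rule nor a risk of abandonment under one.

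This should be fixed because it governs how the full trial is sized and what the pilot may conclude. It does not affect the pilot's conduct, safety or feasibility criteria.

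**What to change.** - **Feasibility outcomes and Sample size calculation:** remove the observed between-arm effect as an input to the power calculation. State that the pilot supplies the SSI rate pooled over arms in the enrolled implant and non-implant mix, plus recruitment and retention. Size the full trial on a pre-stated minimum important reduction, with a sensitivity table over plausible control rates and reductions; the pooled rate is itself known only to about ±6 points.
- **Statistical analysis:** state that the SSI comparison is exploratory, and report the difference with its 95% confidence interval.
- **Abstract, Discussion:** replace the sentence on robust evidence with the feasibility aim in Study objectives, and bring the effectiveness aim in the main Discussion into line.

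The cost is rewording and a more modest claim. Patients, visits and data collection do not change. The investigators would also have to agree a minimum important reduction, which the full trial needs in any case.
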